### 2.4. Statistical analyses

In the case of quantitative data, we will calculate the mean, standard deviation, and confidence interval as well as the minimum, maximum, P25, P50, and P75, as needed. For count data, we will calculate the frequency distributions and corresponding percentages. For rank data, we will provide frequency distributions and percentages, as well as median and mean rankings. Qualitative data will be presented as the positive rate, positive number, and denominator number of cases. Data from MoCA-BJ, AVLT, SDMT, DST, HAMA, and ADL will be analyzed by repeated-measures ANOVA using SPSS software (version 25.0; IBM, Armonk, NY, USA). Repeated-measures ANOVA will be used to analyze the differences between time points and groups. The acquired EEG signals will be analyzed offline using MATLAB2013b. The EEGLAB toolbox (version 13.0.0b) will be used for EEG data preprocessing (Delorme and Makeig, 2004), followed by interest channel selection based on the average level of the two groups and the relative spectral energy extracted from each frequency band. Finally, we will use repeated-measures ANOVA to compare the differences between groups and the relative spectral energy at different times. Statistical significance will be set at *P* < 0.05.

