**Methods:**

The study protocol is designed as a single-center, double-blind, randomized controlled trial. Forty patients with PSCI will be randomly assigned to two different TMS groups, one with iTBS and the other with 5 Hz rTMS. Neuropsychological evaluation, activities of daily living, and resting electroencephalography will be conducted before treatment, immediately post-treatment, and 1 month after iTBS/rTMS stimulation. The primary outcome is the change in the Montreal Cognitive Assessment Beijing Version (MoCA-BJ) score from baseline to the end of the intervention (D11). The secondary outcomes comprise changes in resting electroencephalogram (EEG) indexes from baseline to the end of the intervention (D11) as well as the Auditory Verbal Learning Test, the symbol digit modality test, the Digital Span Test findings, and the MoCA-BJ scores from baseline to endpoint (W6).

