**Discussion:**

In this study, the effects of iTBS and rTMS will be evaluated using cognitive function scales in patients with PSCI as well as data from resting EEG, which allows for an in-depth exploration of underlying neural oscillations. In the future, these results may contribute to the application of iTBS for cognitive rehabilitation of patients with PSCI.

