##### 2.1.2.1. Inclusion criteria

• Age 18 to 80 years;

• Stroke patients meeting the diagnostic criteria established at the Fourth National Cerebrovascular Disease Academic Conference in 1995;

• Imaging evidence of stroke confirmed by computed tomography (CT) or magnetic resonance imaging (MRI);

• Montreal Cognitive Assessment Scale (MoCA) score ≤24;

• Cognitive impairment should occur within 12 months of the vascular event and last for at least 3 months;

• First-ever stroke;

• Right-handed;

• Normal cognitive function before stroke;

• No severe aphasia (screened by the Chinese Aphasia Battery) and capable of completing cognitive tests;

• Stable vital signs;

• Voluntary participation and signed informed consent (signed by the patient or another authorized representative).

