#### 2.2.2. iTBS protocol

The iTBS parameters include three continuous pulses at 50 Hz, repeated at 5 Hz (2 s on, 8 s off) for a total of 192 s and 600 pulses. After the stimulation is completed, the direction of the coil is turned 90°, and a sham stimulation lasting 408 s is conducted in order to ensure the consistency of treatment time such that all patients are blinded to the experimental protocol.

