#### 2.2.4. Routine medical care

Medical care based on the disease of each patient is permitted.

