### 2.3. Outcomes

Our primary outcome will be the Montreal Cognitive Assessment Beijing Version (MoCA-BJ) score from baseline to the end of the intervention (D11). Secondary outcomes will be resting EEG indexes, the Auditory Verbal Learning Test (AVLT), the symbol digit modality test (SDMT), the Digital Span Test (DST), and adverse events. Indexes of resting EEG include the absolute power and relative power of neural oscillations. Other outcomes include the Hamilton Depression Scale (HAMD) and Activities of Daily Living (ADL). All clinical assessments will be performed thrice: pre-treatment (baseline), post-last treatment, and at the 1-month follow-up. An experienced physician will conduct all cognitive assessments throughout the study and will be blinded to the participants’ group assignment and trial phases. The resting EEG will be conducted at baseline and at the end of TMS treatment.

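### With two active arms and no control, the time effect tested in section 2.4 cannot be attributed to TMS; the between-arm contrast in change should be named as the only inferential test

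*Protocol article*

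**What the plan says.** The abstract's Methods paragraph sets out the arms: "Forty patients with PSCI will be randomly assigned to two different TMS groups, one with iTBS and the other with 5 Hz rTMS". The only sham element is in section 2.2.2, where after active iTBS "a sham stimulation lasting 408 s is conducted in order to ensure the consistency of treatment time". It equalises session length and is not a control condition.

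The primary outcome is change in MoCA-BJ from baseline to D11 (abstract; section 2.3). Section 2.4 gives the analysis of the scales: "Repeated-measures ANOVA will be used to analyze the differences between time points and groups". The EEG sentence follows the same pattern, comparing groups and comparing relative spectral energy across times. One threshold covers everything: "Statistical significance will be set at *P* < 0.05". The group-by-time interaction is not named.

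On what the trial is for, the article speaks in two ways. The abstract's Introduction, section 1 and the end of section 3 state a comparative aim, the difference between iTBS and rTMS. The abstract's Discussion says that "the effects of iTBS and rTMS will be evaluated using cognitive function scales in patients with PSCI". Section 2.3.2 plans EEG contrasts before against after treatment, and section 3 hopes to study the facilitating effect of TMS on cognition and the neural changes that underlie the interventions.

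On the setting, patients are inpatients of a rehabilitation ward (section 2.1.1). Section 2.2.4 says "Medical care based on the disease of each patient is permitted". Section 2.1.2.1 requires that "Cognitive impairment should occur within 12 months of the vascular event and last for at least 3 months". On testing, section 2.3 says "All clinical assessments will be performed thrice". The limitations paragraph names the single centre, the small sample and differing medication. It does not name the lack of a control arm.

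**The concern.** Of the two effects that section 2.4 names, neither is the one the primary outcome calls for.

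The time effect is a before-after comparison in patients who all receive TMS, so randomisation does not protect it. Anything that moves both arms together enters it in full: recovery, ward care and familiarity with the tests. The group main effect is protected by randomisation, but it averages the baseline visit into the comparison and so dilutes any difference in change.

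A significant time effect with no difference between arms is a plausible result of a small comparison of two active modes. The plan does not say how that result is to be read, and the wording on TMS effects points towards reading it as benefit from both modes. The same gap bears on the aim in section 3 of showing iTBS to be non-inferior. Without a control, similar change in both arms cannot distinguish two treatments that work from two that do not.

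**Working it through.** **1. The plan's own figure.** Section 2.1.4 gives a minimum of 32 in total for a repeated-measures ANOVA, between factors, with effect size f = 0.25, alpha 0.05 and power 85%, then 40 after 20% loss (32/0.8 = 40). The number of measurements m and their correlation ρ are not stated; I take m = 3 and ρ = 0.5.

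- Between factors: λ = f²·N·m/(1+(m−1)ρ) = 0.0625×32×3/2 = 3.0, df 1 and 30, power 0.39. Reaching 85% needs N = 98.
- Within factors (time), or group by time: λ = f²·N·m/(1−ρ) = 0.0625×32×3/0.5 = 12.0, df 2 and 60, power 0.87. The minimum N is 32.

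Under these assumptions 32 matches the time or interaction test and not the between-factors test that is named. The sample size is a separate matter. It bears on this point only because at N = 32 the trial has far more power for a time effect than for a group main effect of the same f.

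**2. How far the group main effect dilutes a difference in change.** Let the arms be equal at baseline and differ by δ afterwards. Averaged over baseline and D11, the group effect is (0+δ)/2 = δ/2. Averaged over three visits with δ sustained to W6, it is (0+δ+δ)/3 = 2δ/3. The contrast in change to D11 estimates δ itself.

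**3. How often a shared shift makes the time test significant.** Assume no TMS effect in either arm and a common mean shift from baseline to D11 of d, in units of the SD of change. The article gives no SD, correlation or practice effect, so d is an assumption. As a translation, a 1-point MoCA gain with an SD of change of 3 or 2 points gives d = 1/3 or 1/2. The test is two-sided at 0.05 with non-centrality d√N and df N−2.

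| d | N = 40: d√N | P(time significant) | N = 32: d√N | P(time significant) |
|---|---|---|---|---|
| 0.20 | 1.26 | 0.23 | 1.13 | 0.20 |
| 0.30 | 1.90 | 0.46 | 1.70 | 0.38 |
| 0.33 | 2.11 | 0.54 | 1.89 | 0.45 |
| 0.50 | 3.16 | 0.87 | 2.83 | 0.78 |

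**4. What the same shift does to the between-arm contrast.** It cancels: (μ+d) − (μ+d) = 0. In a simulation of 20,000 trials with 20 per arm, the group-by-time test rejected in 5.2%, 5.0% and 5.0% of runs at shared shifts of 0, 0.5 and 1.0 SD. At 0.5 SD the time test rejected in 87%.

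**The case against.** The strongest reply is that the trial is comparative and says so in the abstract's Introduction, section 1 and section 3. An active comparator is a legitimate design for that aim, shared drift cancels in it, and the study is labelled pilot and exploratory. Section 2.4 merely lists the factors of an ANOVA. All of this stands, and it is why the point is moderate and why no extra arm is asked for.

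A reader might go further in several ways that the documents do not support:

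- That the plan will treat a significant time effect as proof of efficacy. No passage sets such a rule. The wording invites that reading but does not prescribe it.
- That care is without limits. Section 2.2.4 permits care for each patient's disease, but section 2.1.2.2 excludes users of antidepressants or psychostimulants.
- That selection on a MoCA of 24 or less adds a known amount of regression to the mean. Table 1 lists the eligibility screen at −D1 and the MoCA assessment at time 0. It is not established that the selecting score is also the baseline score, so I count nothing for this.
- That marked spontaneous recovery is to be expected. Impairment must already have lasted at least 3 months and the primary interval is about 11 days. Recovery is possible but not shown.
- That identical test forms will be reused. The article is silent on this, and an article may leave such detail to the full protocol.

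It is also fair to say that the percentages in step 3 follow from a shift that was put in by hand. They show how easily a modest shared change would reach significance, not that it will occur.

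**Conclusion.** The point holds in a limited form. Section 2.4 tests time at P<0.05 in a design where that effect cannot be attributed to TMS, and it leaves unnamed the contrast that answers the primary question. If nothing but a shared shift of 0.33 to 0.5 SD of change occurred, about 54% to 87% of trials of 40 would show a significant time effect (45% to 78% with 32). The shift is assumed; at 0.2 SD the figure for 40 patients falls to 23%.

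The randomised comparison of iTBS with rTMS is not biased by this. What is at risk is the interpretation of within-arm changes in the scales and the EEG, and of similar change in both arms under the non-inferiority aim. Severity is moderate.

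**What to change.** - **Section 2.4:** name the between-arm contrast in change as the only inferential test, either as group by time or as a baseline-adjusted difference, iTBS minus rTMS. For the scales, use D11 as primary and W6 as secondary. For EEG, use D11, the only post-baseline recording in Table 1 and section 2.3.
- **Section 2.4:** report time main effects and within-arm changes, cognitive and EEG, descriptively with confidence intervals and without a claim of efficacy.
- **Abstract, Discussion:** say that the difference between iTBS and rTMS will be evaluated, in line with the aim stated elsewhere.
- **Limitations paragraph of section 3:** add that, with no control arm, similar change in both arms does not show that either treatment works.

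This costs a few sentences and needs no further patients, visits or staff. The price is that the trial gives up within-arm efficacy claims, which the design could not support in any case.

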#### 2.1.4. Sample size

This will be an exploratory study. The required sample size for this study was estimated using GPower software (version 3.1.9.7) (Faul et al., 2007). Repeated measures analysis of variance (ANOVA) will be used for statistical analysis, with group and time as affecting factors. Accordingly, the *F*-test (repeated-measures ANOVA, between factors) was chosen, with a power of 85%, an alpha value of 0.05, and an effect size of 0.25 (Cunningham and Mccrum-Gardner, 2007). The predicted minimum sample size was 32 (two groups) considering a 20% loss to follow-up. Therefore, we set the sample size at 40 patients in total, with 20 patients in each group.

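### The primary outcome is the MoCA-BJ change to D11, but the only stated analysis is a three-visit repeated-measures ANOVA in which no named term isolates the D11 difference between arms

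*Protocol article*

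**What the plan says.** The abstract states: "The primary outcome is the change in the Montreal Cognitive Assessment Beijing Version (MoCA-BJ) score from baseline to the end of the intervention (D11". Section 2.3 has the same time point: "Our primary outcome will be the Montreal Cognitive Assessment Beijing Version (MoCA-BJ) score from baseline to the end of the intervention (D11". Section 2.3 also sets the visits: "All clinical assessments will be performed thrice: pre-treatment (baseline), post-last treatment, and at the 1-month follow-up". Table 1 agrees, listing MoCA at baseline, D11 and W6. The abstract makes the MoCA-BJ change to W6 a secondary outcome.

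Section 2.4 gives one method for MoCA-BJ and the other scales: "Repeated-measures ANOVA will be used to analyze the differences between time points and groups". Section 2.1.4 describes the same model: "Repeated measures analysis of variance (ANOVA) will be used for statistical analysis, with group and time as affecting factors". For the sample size it says that the F-test option ("repeated-measures ANOVA, between factors) was chosen") was used, with 85% power, alpha 0.05 and effect size 0.25. This gave a minimum of 32, raised to 40 (20 per arm) for 20% loss.

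**The concern.** The primary outcome concerns one time point and one comparison: the difference between arms in change to D11. The stated ANOVA covers three visits and can yield a group effect, a time effect and a group-by-time interaction. None of these is that comparison:

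- The group effect averages over all visits, including baseline, where randomisation makes the expected difference zero.
- The time effect compares no treatments.
- The interaction over three visits has 2 degrees of freedom and can be significant because of W6 alone.

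The P value reported as primary could therefore answer a different question from the one posed, with less power in a trial of 40. The Discussion also wants to judge whether iTBS is non-inferior or superior to rTMS. That calls for an estimated D11 difference with a confidence interval, which an overall F-test does not supply.

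**Working it through.** **Inputs from the protocol article.** Three visits (section 2.3, Table 1); 20 per arm, 20% loss, alpha 0.05, effect size f = 0.25, power 85%, minimum N = 32 (section 2.1.4). After the planned loss, 20 × 0.8 = 16 per arm.

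**Assumptions, not in the documents.** D11 difference d = 0.75 SD; W6 effect either sustained, halved or gone; equal variances and one common between-visit correlation ρ of 0.5, 0.7 or 0.8; two-sided tests.

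**Step 1: the plan's own N.** m is the number of visits.

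- Between factors (group main effect): λ = f²·N·m / (1 + (m−1)ρ), df 1 and N−2. At N = 32, m = 3, ρ = 0.5: λ = 0.0625 × 32 × 3 / 2 = 3.0, power 39%. Reaching 85% takes N = 98 (50 at ρ = 0, 128 at ρ = 0.8). The stated option does not return 32.
- Within-between interaction: λ = f²·N·m / (1−ρ), df m−1 and (N−2)(m−1). At the same values λ = 6 / 0.5 = 12, power 86.6%; N = 30 gives 84.1%. So 32 is the smallest even N, and 32 / (1 − 0.2) = 40.

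The label therefore points to the group main effect and the number to the interaction. Both have to be examined.

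**Step 2: if the group main effect decides.** The expected differences at the three visits are 0, d and r·d, where r is the share of the effect left at W6. Their mean is d(1+r)/3: 2d/3 if sustained, d/3 if gone by W6. The variance of a three-visit mean is SD²(1+2ρ)/3. For ANCOVA at D11 the signal is d and the variance SD²(1−ρ²). With n = 20 per arm, ρ = 0.5, sustained effect:

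- Main effect: 0.50 / √(0.667 × 2/20) = 1.94, 38 df, power 47%.
- ANCOVA: 0.75 / √(0.75 × 2/20) = 2.74, 37 df, power 76%.

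The ratio of required sample sizes is [(1+2ρ)/3] / (2/3)² / (1−ρ²). This is 0.667 / 0.444 / 0.75 = 2.0 at ρ = 0.5, and 0.8 / 0.444 / 0.51 = 3.5 at ρ = 0.7.

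**Step 3: if the interaction decides.** λ = (n/2)·Σ(δⱼ − δ̄)² / (1−ρ), with 2 and 2(N−2) = 76 df. Here δⱼ are the visit differences in SD units and δ̄ is their mean.

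- Sustained effect (0, 0.75, 0.75): the sum of squares is 0.375. At ρ = 0.5, λ = 10 × 0.375 / 0.5 = 7.5, power 67%.
- Halved by W6 (0, 0.75, 0.375): the sum of squares is 0.281, λ = 5.6, power 54%.

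**Results, d = 0.75 SD:**

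| Per arm | W6 effect | ρ | Group main effect | 3-visit interaction | D11 ANCOVA |
|---|---|---|---|---|---|
| 20 | sustained | 0.5 | 47% | 67% | 76% |
| 20 | sustained | 0.7 | 41% | 88% | 90% |
| 20 | sustained | 0.8 | 38% | 97.5% | 97.1% |
| 20 | halved | 0.5 | 29% | 54% | 76% |
| 20 | halved | 0.7 | 25% | 77% | 90% |
| 20 | gone | 0.5 | 16% | 67% | 76% |
| 20 | gone | 0.7 | 14% | 88% | 90% |
| 16 | sustained | 0.5 | 39% | 56% | 66% |
| 16 | sustained | 0.7 | 33% | 79% | 82% |

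**Step 4: a plain D11 change score.** Variance 2·SD²(1−ρ), same signal d. Power at 20 per arm is 64% (ρ = 0.5) and 85% (ρ = 0.7). It targets the right quantity but has less power than ANCOVA.

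**The case against.** The strongest reply is that a group-by-time analysis is the ordinary use of this design. Section 2.4 does not say that the group main effect decides, and N = 32 fits the interaction. This stands. A reader might infer that the planned analysis necessarily dilutes the treatment effect, or that the trial was sized on the main effect. The documents do not support either inference: the only evidence for the main effect is the option label in section 2.1.4, and that option does not yield 32. The interaction tests differential change and is not diluted by baseline. Against it, the power gain from ANCOVA for a sustained effect is small and vanishes near ρ = 0.8.

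The second reply is that ANCOVA is not the only matching test, since a D11-minus-baseline contrast would also target the primary outcome. That stands too; ANCOVA is preferred for efficiency.

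The third is that this is a condensed article about an exploratory trial, and the contrast may be fixed in a full protocol or SAP. That would excuse silence. Here the article states an analysis and a significance level, and the analysis as described does not isolate the primary outcome.

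A reader might also extend the three-visit argument to EEG. Table 1 and section 2.3 schedule EEG at baseline and D11 only, and the abstract defines the EEG outcome over that interval. With two visits the interaction is already the comparison of change. (The abstract and section 2.1.3 also mention EEG at about W6; that inconsistency is a separate matter.)

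**Conclusion.** The mismatch holds on the text: a D11 primary outcome is paired with a three-visit ANOVA, and neither section 2.1.4 nor section 2.4 names a term for the D11 difference between arms. How much it costs depends on which term would decide.

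- **Group main effect:** the loss is large. Power falls by 29 points at ρ = 0.5 (76% to 47%) and by 49 points at ρ = 0.7 (90% to 41%) with 20 per arm and a sustained effect. With 16 per arm the losses are 27 and 49 points.
- **Interaction:** the fault is chiefly one of target, because W6 enters a D11 question. The ANCOVA gain is 9 points at ρ = 0.5, 2 at 0.7 and about none at 0.8 if the effect is sustained. It is 22 and 13 points at ρ = 0.5 and 0.7 if the effect halves by W6.

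The fractions 2d/3 and d/3 are arithmetic and do not depend on the SD. Every power figure rests on the assumed 0.75 SD effect, the assumed correlations and equal variances, because the documents give no MoCA-BJ SD, between-visit correlation or target difference.

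**What to change.** In section 2.4, name one primary analysis: ANCOVA of D11 MoCA-BJ on randomised group with baseline MoCA-BJ as covariate, reporting the adjusted difference and its 95% CI. Analyse W6 MoCA-BJ as a secondary contrast. State that neither the group main effect nor the time main effect will be used as evidence on iTBS versus rTMS.

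The same baseline-adjusted form can serve AVLT, SDMT and DST. For EEG at two visits it brings only an efficiency gain over the interaction.

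The cost is one paragraph of wording and one degree of freedom. The baseline score is already collected and the planned software can fit the model. The change should be made before the data are unblinded, so that no choice among group, time and interaction P values remains.

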## 3. Discussion

Transcranial magnetic stimulation modulates brain function through neural changes induced by magnetic pulses. Using pulsed magnetic fields, TMS regulates the action potentials of nerve cells by inducing current in the central nervous system. This approach can affect the metabolic and neurophysiological activities of the brain. In recent decades, TMS has been widely used to treat cognitive impairment caused by various neurological, psychiatric, and psychological disorders, including stroke, Alzheimer’s disease, Parkinson’s disease, and schizophrenia. While iTBS, a new model of TMS, has been proven to be effective in Parkinson’s disease with cognitive impairment, its use in patients with PSCI is unclear. Several studies have shown that rTMS is a safe and effective method for improving cognitive function (Chou et al., 2020; Jiang et al., 2020; Alyagon et al., 2021). Regarding neurophysiology, iTBS may have equal or greater excitatory effects than conventional TMS (Di Lazzaro et al., 2011; Bakker et al., 2015). However, previous evidence indicates that conventional high-frequency TMS facilitates neurogenesis in the motor cortex more effectively than iTBS in a rat model (Luo et al., 2017). Another study that applied rTMS to healthy individuals found that rTMS produced a greater response than iTBS (Curtin et al., 2017). In patients with PSCI, there is no consensus regarding whether conventional rTMS or iTBS is more effective.

To assess the effect of the treatment, neurobehavioral scales are often used in studies of PSCI (Tsai et al., 2020). However, scale results are sometimes, to some extent, subjective because of the evaluator’s judgment and the state of the patient (Tsai et al., 2020). Therefore, objective means of assessment are urgently needed. EEG is gaining increasing attention because it is a special and complex bioelectrical signal reflecting the functional state of the brain, with the advantages of high temporal resolution, non-invasiveness, and low cost. A direct effect of rTMS treatment on brain function is altered nerve oscillation, which can have a therapeutic effect by resetting the oscillations of the thalamus and cortex (Thut et al., 2011; Veniero et al., 2011; Chota et al., 2021). Rhythmic patterns of neural oscillations are believed to play a functional role in local processing and communication among neuronal systems (Fries, 2005; Thut et al., 2012). Different regions of the human cortex tend to oscillate at different frequencies. Thus, it is possible to study neural oscillation activity in more detail. Most cognitive processes are associated with a frequency band in the delta, theta, alpha, beta, or gamma range. Several researchers have suggested, based on high-quality correlative EEG data, that brain oscillations are involved in a variety of sensory and cognitive processes (Klimesch, 1999; Lu et al., 2022). However, a causal relationship can only be demonstrated by directly modulating the oscillatory signals. EEG is an effective and dependable tool for detecting neural oscillations in the brain. Thus, this study may be able to investigate the specific relationship between neural oscillations and TMS facilitative effects on cognitive function in more detail.

In conclusion, the goal of this study will be to compare effect differences among various TMS protocols (iTBS and conventional rTMS) on PSCI and analyze whether iTBS is non-inferior or superior to conventional rTMS treatment. Given that iTBS has a shorter treatment time, it is more convenient to use if its therapeutic effect is not inferior to that of rTMS. Thus, iTBS might prove more advantageous and convenient than the classic rTMS for outpatients. Furthermore, we hope to explore the neural activity changes underlying iTBS/rTMS intervention in PSCI and thus, provide a theoretical foundation for clinical applications.

This study has some limitations. It will be a single-center trial with a comparatively small sample size, due to recruitment difficulties associated with the management of coronavirus disease 2019. In addition, the heterogeneity of oral medication in patients with PSCI may also pose potential problems in measuring cortical excitability and therapeutic response (Cantone et al., 2020). Future multi-center studies should be conducted to mitigate these limitations.

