## Abstract

**Introduction:**

Intermittent theta burst stimulation (iTBS), a novel mode of transcranial magnetic stimulation (TMS), has curative effects on patients with post-stroke cognitive impairment (PSCI). However, whether iTBS will be more applicable in clinical use than conventional high-frequency repetitive transcranial magnetic stimulation (rTMS) is unknown. Our study aims to compare the difference in effect between iTBS and rTMS in treating PSCI based on a randomized controlled trial, as well as to determine its safety and tolerability, and to further explore the underlying neural mechanism.

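### The stated goal includes non-inferiority of iTBS to rTMS, but the sample size and analysis contain only an ANOVA test of difference, with no margin and no confidence-limit rule

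*Protocol article*

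**What the plan says.** **Goal.** The closing part of the protocol article's section 3 (Discussion) says the study will "analyze whether iTBS is non-inferior or superior to conventional rTMS treatment". The next sentence gives the practical reason: iTBS is shorter, so "it is more convenient to use if its therapeutic effect is not inferior to that of rTMS". The Abstract states the aim more narrowly: "Our study aims to compare the difference in effect between iTBS and rTMS in treating PSCI".

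**Analysis.** Section 2.4 gives one inferential method for MoCA-BJ and the other clinical scales: "Repeated-measures ANOVA will be used to analyze the differences between time points and groups". The criterion is "Statistical significance will be set at *P* < 0.05", with sidedness not stated. A confidence interval appears only among the descriptive summaries of quantitative data ("we will calculate the mean, standard deviation, and confidence interval"). It is not tied to the between-group difference or to any limit.

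**Sample size.** Section 2.1.4 calls the study exploratory and uses an F-test: "repeated-measures ANOVA, between factors) was chosen, with a power of 85%, an alpha value of 0.05, and an effect size of 0.25". This gives 32 patients, set at 40 (20 per group) for 20% loss. No margin enters the calculation.

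**The concern.** A test of difference asks whether the data are incompatible with equal effects. Non-inferiority asks whether they rule out a deficit larger than a stated amount. The second question needs that amount, and a confidence limit or one-sided test set against it. The plan has neither, so half of the stated goal has no analysis behind it.

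This is more than a detail that an article may leave to an analysis plan. The margin determines the sample size, and the article presents a sample-size calculation made for a difference. A margin added later would leave 40 patients justified for a different question.

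At stake is the conclusion that matters most for practice. If P exceeds 0.05, a report could say that iTBS is as good as rTMS and quicker, although the trial would often give that P value when iTBS is worse.

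**Working it through.** **Inputs from the document.** Two groups; 32 evaluable (16 per arm) to 40 (20 per arm); three assessments (baseline, D11, W6); f = 0.25; power 85%; alpha 0.05.

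**Assumptions.** The document gives no SD, correlation or margin. Results are therefore in SD units of MoCA-BJ, with a common correlation ρ of 0.5 to 0.7 between visits and two-sided 5% tests. For two equal groups d = 2f, so f = 0.25 is read as 0.5 SD.

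**1. The plan's own figure.**
- Between-factors option, as named: λ = f²Nm/(1+(m−1)ρ). With N = 32, m = 3, ρ = 0.5, λ = 0.0625×32×3/2 = 3.0 on 1 and 30 df, and power is 39%. Reaching 85% needs N = 98 (50 at ρ = 0; 118 at ρ = 0.7).
- Interaction (or within-factors) option: λ = f²Nm/(1−ρ) = 0.0625×32×3/0.5 = 12 on 2 and 60 df. Power is 86.6%, which reproduces 32. Then 32/0.8 = 40.

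Which option was run is a separate matter. Either way the calculation is for a difference, with no margin.

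**2. Chance of P > 0.05 when iTBS is truly 0.5 SD worse at D11 and W6.** The between-group differences at the three visits are 0, 0.5 and 0.5. The formulas below are filled in for n = 16 per arm and ρ = 0.5.
- Group main effect: averaged difference (0+0.5+0.5)/3 = 0.333; SE = √[((1+2ρ)/3)(2/n)] = 0.289; noncentrality 1.155 on 30 df.
- Group-by-time interaction: λ = (n/2)Σ(δⱼ−δ̄)²/(1−ρ) = 8×0.1667/0.5 = 2.67 on 2 and 60 df.
- Baseline-adjusted D11 comparison (not in the plan, shown because D11 is primary): SE = √[(1−ρ²)(2/n)] = 0.306; noncentrality 0.5/0.306 = 1.63 on 29 df.

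| n per arm, ρ | Main effect | Interaction | Adjusted D11 |
|---|---|---|---|
| 16, 0.5 | 80% | 72% | 65% |
| 16, 0.7 | 82% | 56% | 52% |
| 20, 0.5 | 76% | 66% | 57% |
| 20, 0.7 | 79% | 47% | 42% |

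**3. What the data could show about non-inferiority.** The 95% CI half-width for the adjusted D11 difference is t(0.975, 2n−3)×SE. The last column is the probability, with identical treatments, that the lower limit lies above −0.5 SD. The 0.5 SD margin is only an illustration.

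| n per arm, ρ | Half-width (SD) | 0.5 SD margin met |
|---|---|---|
| 16, 0.5 | 2.045×0.306 = 0.63 | 35% |
| 16, 0.7 | 2.045×0.252 = 0.52 | 48% |
| 20, 0.5 | 2.026×0.274 = 0.55 | 43% |
| 20, 0.7 | 2.026×0.226 = 0.46 | 58% |

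If the MoCA-BJ SD were 3 to 5 points (an assumption), the half-width would run from 0.46×3 = 1.4 to 0.63×5 = 3.1 points.

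**4. Size needed for that margin.** At 85% power and one-sided 2.5%, an unadjusted comparison needs 2(1.960+1.036)²/0.5² = 71.8, or 72 per arm: 144 evaluable, and 144/0.8 = 180 recruited. Here the margin is in SDs of the quantity compared; at ρ = 0.5 the change score and the score have the same SD. Baseline adjustment multiplies 71.8 by 1−ρ², giving 54 per arm at ρ = 0.5 and 37 at ρ = 0.7. All exceed 16 to 20 per arm.

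**The case against.** The best defence is context. The title calls the trial a pilot and section 2.1.4 calls it exploratory. The Abstract and Introduction state the aim only as comparing effects. The non-inferiority wording comes late in the Discussion, the convenience argument is conditional, and the limitations concede a small sample. Section 2.4 also mentions confidence intervals, so the data for an interval-based reading will exist. All this is true, and it lowers the severity. It does not remove the mismatch: the Discussion presents non-inferiority as part of this study's goal, the limitations do not withdraw it, and the planned interval is not linked to the treatment difference or to a margin.

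Three stronger readings are tempting, and the documents do not support them.
- A reader might infer that the investigators will treat P > 0.05 as proof of non-inferiority. The article nowhere says so; it speaks of analysing the question, not of deciding it by that rule. What can be said is that no valid route is given and a null result could be misread.
- A reader might infer that a worse iTBS would nearly always escape detection. At 0.5 SD the probability runs from 42% to 82%, depending on test, correlation and numbers. At 0.8 SD, an unadjusted two-group comparison would be non-significant about 41% (16 per arm) or 31% (20 per arm) of the time.
- A reader might take the CI half-width as the smallest margin that could be met. The point estimate varies, so a narrower margin can be met by chance; power for it is low.

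**Conclusion.** Wrong as written; should fix. One half of the stated goal cannot be answered by the stated design and analysis. A non-significant ANOVA would be weak evidence: with a true deficit equal to the plan's own effect size, it would occur in roughly four trials in five on the group main effect, and in about 42% to 72% on the other two analyses. With truly identical treatments, an assumed 0.5 SD margin would be met in only about 35% to 58% of trials, even with baseline adjustment.

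The mismatch itself rests on the text alone. The percentages rest on f = 0.25 read as 0.5 SD, 16 to 20 evaluable patients per arm, an assumed common correlation of 0.5 to 0.7 and, for the last range, the illustrative margin. The exploratory pilot status and the wording-only remedy keep this below a must-fix.

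**What to change.** Remove non-inferiority from the goal in the Discussion and reword the convenience argument to match. In section 2.4, state that the main result is the iTBS-minus-rTMS difference in D11 MoCA-BJ with its two-sided 95% CI, reported as exploratory, and that P > 0.05 will not be interpreted as non-inferiority or equivalence.

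If the sponsor wishes to keep the claim, it should fix and justify a MoCA-BJ margin before unblinding, conclude non-inferiority only if the lower 95% limit lies above minus that margin, and state that power for this is low with 40 patients.

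The first option changes wording in two sections; randomisation, assessments and data collection stay as they are. The cost is a more modest claim.
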